## 10 SAFETY

### 10.1 GENERAL RULES – INSTRUCTIONS

Safety management will be conducted according to the French regulatory requirements (Law No. 2012-300 of 05/03/2012 as amended by Ordinance No. 2016-800 of 16 June 2016).

### 10.2 DEFINITIONS

#### 10.2.1 Adverse Event (AE)

Any untoward medical occurrence in a patient or clinical investigation subject administered a pharmaceutical product and which does not necessarily have a causal relationship with this treatment. An adverse event (AE) can therefore be any unfavorable and unintended sign (including an abnormal laboratory finding), symptom, or disease temporally associated with the use of a medicinal (investigational) product, whether or not considered related to it.

#### 10.2.2 Adverse Reaction

All untoward medical occurrence in a patient or clinical investigation subject which participate to research involving the human person **related to the study procedure or to the experimental product**.

All untoward responses to an investigational medicinal product related to any dose administered.

#### 10.2.3 SERIOUS Adverse event

A serious adverse event (SAE) is an AE that fulfils one or more of the following criteria:

- Results in death
- Is immediately life-threatening
- Requires in-patient hospitalization or prolongation of existing hospitalization
- Results in persistent or significant disability or incapacity

- Is a congenital abnormality or birth defect
- Is an important medical event\*.

\* Medical and scientific judgment should be exercised in deciding whether expedited reporting is appropriate in other situations, such as important medical events that may not be immediately life-threatening or result in death or hospitalization but may jeopardize the patient or may require intervention to prevent one of the other outcomes listed in the definition above. These should also usually be considered serious.

Some “hospitalization/prolonged hospitalization” are not considered to be reported as serious adverse event:

- Admission for administrative or social reasons
- Hospitalization predefined by the protocol
- Hospitalization for medical or surgical treatment planned before the beginning of the trial
- Passage to day hospital
- Hospitalizations for pre-existing signs and symptoms that have not been aggravated

These have not to be notified as SAE.

#### 10.2.4 Suspected Unexpected Adverse Reaction

Any serious adverse reaction for which the nature, severity, frequency or outcome is not consistent with the applicable product information (e.g investigator’s brochure for an unauthorized investigational product or summary of product characteristics for an authorised product).

Any serious adverse reaction for which the nature, severity, frequency or outcome is not consistent with the applicable product information, diagnostic or therapeutic study mandated procedure (non-invasive and/or invasive) evaluated in the protocol.

### 10.3 INVESTIGATOR’S RESPONSIBILITIES

#### 10.3.1 Detection and registration of adverse events

All adverse events have to be searched, reported and recorded, processed and evaluated.

All adverse events occurring, once the informed consent form has been signed, **during treatment and 30 days after the last study drug administration**, must be recorded by the investigator.

The intensity of the events will be estimated according to the NCI-CTCAE version 5.0 classification (grade 1 to 5 toxicity). The intensity of adverse events not listed in this classification will be graded as follows:

- **Grade 1: mild** : Discomfort noticed but no disruption of normal daily activity
- **Grade 2: moderate** : Discomfort sufficient to reduce or affect daily activity; no treatment or medical intervention is indicated although this could improve the overall well-being or symptoms of the patient
- **Grade 3: severe** : Inability to work or perform normal daily activity; treatment or medical intervention is indicated in order to improve the overall well-being or symptoms; delaying the onset of treatment is not putting the survival of the patient at direct risk
- **Grade 4: Life-threatening/disabling** : An immediate threat to life or leading to a permanent mental or physical conditions that prevents work or performing normal daily activities; treatment or medical intervention is required in order to maintain survival
- **Grade 5: Death AE or resulting in death**

The investigator will specify for each event:

- ✓ The seriousness
- ✓ The date of start +/- the date of end of the event
- ✓ The duration
- ✓ The intensity
- ✓ The causality assessment
- ✓ The outcome

If a SAE occurs, the sponsor should be notified of the event awareness by the investigator without any delay. This will be done by mailing sponsor's Serious Adverse Event Report Form.

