### 112 3 STUDY FLOW CHART

|                                                                                                                       | Before inclusion         | Before Surgery           | Surgery                     | At 1 and 6 months post-surgery |
|-----------------------------------------------------------------------------------------------------------------------|--------------------------|--------------------------|-----------------------------|--------------------------------|
| Informed Consent                                                                                                      |  |                          |                             |                                |
| History of the disease                                                                                                |  |                          |                             |                                |
| Physical examination (weight, height)                                                                                 |  |                          |                             |                                |
| Pregnancy test (urine or blood)
(within the previous 8 days)                                                       |  |                          |                             |                                |
| Cervical ultrasound                                                                                                   |  |                          |                             |                                |
| Blood tests*                                                                                                          |  |                          |                             |        |
| F18-choline PET-CT and/or MIBI SPECT-CT
(within 12 weeks prior to surgery; at least 48 hours between the 2 exams)  |                          |  |                             |                                |
| For patients undergoing a PET-choline examination, a telephone call the day after the examination to assess tolerance |                          |  |                             |                                |

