| Adverse events                                                                                                        |                          |  |     |        |
| Patient satisfaction (EVAN-G questionnaire)                                                                           |                          |                          |  ** |                                |

113  
114 \* Biochemistry: Calcium, phosphoremia, albumin, creatinine, PTH, 25 OH vitamin D

115 \*\*completed within 4 to 48 hours after surgery, before discharge from hospitalization

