## 6.2 SECONDARY ENDPOINTS

The secondary endpoints are:

- Average cost of caring for a patient for each of the two strategies
- Sensitivity, specificity, error rates, positive and negative likelihood ratios of FCH PET/CT and MIBI SPECT/CT
- Rate of minimally invasive surgeries and bilateral cervical explorations for each diagnostic strategy
- Number of failures of parathyroid surgery (regardless of the type of surgery performed), defined by the persistence of primary hyperparathyroidism 6 months after surgery
- Complications occurring within one month of surgery: infections, hematomas, laryngeal recurrent nerve injury
- Cohen's kappa coefficients between the 2 independent readers, during their first reading, then during their second reading (3 months later); as well as between the first and second reading of each of the 2 readers
- Serum PTH concentration at baseline
- To compare detection sensitivities of FCH PET-CT at 10 min and 60 min post-injection, as well as semi-quantitative analysis.
- Scores for the 6 dimensions (comfort, attention, information, pain management, waiting times, intimacy) of the EVAN-G questionnaire administered perioperatively (4 to 48 hours after the intervention before discharge from hospitalization)

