#### ❖ **Parathyroid Surgery**

It will be performed no later than 12 weeks after the last scintigraphic examination (MIBI SPECT/CT or FCH PET/CT).

Depending on the results of the imaging tests, the surgical procedure will consist of minimally invasive surgery or bilateral cervical exploration. The sample will be sent for extemporaneous examination during surgery.

A nasofibrosopic check-up will be performed postoperatively before discharge from hospitalization to assess the mobility of the vocal cords.

Patient satisfaction in the perioperative period will be assessed using the EVAN-G questionnaire within 48 hours of the procedure.

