## 8 PHARMACEUTICAL FORM OF STUDY MEDICATIONS

### 8.1 MIBI

#### 8.1.1 Introduction to the RPM

**Technetium-99 m-labelled Sestamibi (2-methoxy-isobutyl-isonitrile)** is in the form of a radiopharmaceutical preparation kit, to be labelled with sodium pertechnetate (Tc99m) solution for injection. 99mTc period: 6.02 hours. Gamma-ray single-photon peak of 140 keV.

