## 9 MEDICO-ECONOMIC STUDY

The medico-economic analysis will be carried out from the point of view of health insurance. From this perspective, only direct hospital costs will be included in the analysis. They will include the costs of diagnosis, the costs of surgery (type of surgical procedure, duration of intervention and hospitalization, anesthesia) and the cost of possible complications (hematomas, infections, damage to the recurrent laryngeal nerve, chronic hypoparathyroidism).

The efficacy endpoint will be the cure rate at one month (normalization of serum calcium at one month post-surgery). An incremental cost-effectiveness ratio will be estimated to establish the average cost needed to cure an additional person by moving from the usual strategy to the new strategy.

A sensitivity analysis of the uncertain parameters of the model will be performed to test the robustness of the cost-effectiveness ratio.

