### 10.3.2 SAE reporting process

The investigator has to report the Sponsor of all serious adverse events occurring, once the informed consent form has been signed, **during treatment and 30 days after the last study drug administration.**

All late Serious Adverse Events and considered as reasonably related to the study treatment(s) or to the study procedure must be reported without delay limitation.

The investigator has to immediately report to the sponsor all serious adverse events with the exception of those that are identified as not requiring immediate reporting in the protocol or the investigator's brochure.

Pharmacovigilant contact : [[contact]](mailto:[contact])

[contact]

**This will be done by mailing sponsor's Serious Adverse Event Report Form, and it will be following by some report, as needed, containing all available information concerning the SAE.**

The investigator will specify for each event:

- ✓ The description as clear as possible according to the medical terminology,
- ✓ The intensity,
- ✓ The date of start and the date of end of the event,
- ✓ Measures taken and the necessity or not for a corrective treatment,
- ✓ If the treatment of the study was discontinued or if dose was modified
- ✓ The outcome: For a non-fatal event, the event should be followed until resolution or return to the initial status or to stabilization of potential sequels,
- ✓ The **causality assessment**: he has to assign a causality of "related to study treatment", if there is a "reasonable possibility" that the study treatment caused the event, or "not related to study treatment" if there is "no reasonable possibility" that the study treatment caused the event. The investigator must also assess whether the serious adverse event is "possibly related" to any study mandated procedure or activity, or others concomitants treatments, or under study or any others disease.

The investigator should also, when possible, attach to the serious adverse event report:

- ✓ A copy of the hospital report/hospitalization prolongation,
- ✓ A copy of the autopsy report,
- ✓ A copy of the results of all additional exams performed, including relevant negative results together with the range of normal laboratory values,
- ✓ Any other document judged useful and pertinent (including imaging)

All these documents should be **anonymized**.

Additional information may be requested by the sponsor.

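### The adverse-event window closes 30 days after the last tracer injection, which contradicts the flow chart and does not match the one-month surgical-complication endpoint

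*Protocol*

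**What the plan says.** Section 10.3.1 obliges the investigator to record all adverse events from consent, "during treatment and 30 days after the last study drug administration". Section 10.3.2 sets the same limit for serious adverse events, with one extension: late serious events judged related to a study treatment or procedure stay reportable with no time limit.

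The part of the protocol headed "PHARMACEUTICAL FORM OF STUDY MEDICATIONS" (section 8) covers only MIBI and FCH, so the last study drug administration is the last tracer injection.

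Four other places bear on the period after surgery:

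- **Timing of surgery (section 7.4.3, Parathyroid Surgery):** "It will be performed no later than 12 weeks after the last scintigraphic examination".
- **Secondary endpoint (section 6.2):** "Complications occurring within one month of surgery: infections, hematomas, laryngeal recurrent nerve injury".
- **Cost analysis (section 9):** hospital costs include "the cost of possible complications". The list there adds chronic hypoparathyroidism to the three complications of section 6.2.
- **Flow chart (section 3):** the row "Adverse events" is ticked before surgery, at surgery, and in the column "At 1 and 6 months post-surgery".

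**The concern.** The safety text starts its clock at the scan, whereas the endpoint and the flow chart follow the operation. A site working from section 10 may stop recording before the patient is operated on; a site working from the flow chart would continue to six months after surgery. The protocol does not say which rule governs.

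The events at stake are those of the complication endpoint and of the complication costs in section 9. If sites follow section 10, a non-serious wound infection or haematoma that appears after discharge may go unrecorded, and the chance of that rises with the delay from scan to surgery. The primary endpoint is not affected: it rests on the surgical decision and on post-operative biochemistry.

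**Working it through.** The protocol states no coverage figure, so there is none to reproduce. The check is a comparison of time windows.

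**Inputs**

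- End of the recording window: 30 days after the last tracer injection (10.3.1, 10.3.2).
- Longest interval from last scan to surgery: 12 × 7 = 84 days (7.4.3). This is a maximum; no expected interval is given.
- Each scan is acquired within 90 minutes of injection or starts at that point (7.4.4), so the scan and injection dates are the same.
- Length of the complication endpoint: one month after surgery (6.2), taken as 30 days.

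**Latest day needed.** 84 + 30 = day 114 after the last tracer, against day 30 in section 10.

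**Share of the post-operative month outside the window.** With surgery *t* days after the last tracer, the share outside is min(*t*, 30)/30.

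| Interval *t* (days) | Calculation | Share outside |
|---|---|---|
| 7 | 7/30 | 23% |
| 14 | 14/30 | 47% |
| 15 | 15/30 | 50% |
| 21 | 21/30 | 70% |
| 28 | 28/30 | 93% |
| 30 to 84 | 30/30 | 100% |

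More than half the month is outside only when surgery comes more than 15 days after the last tracer.

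**Average over patients.** This needs a distribution of intervals, which the protocol does not give. As an assumption, take intervals uniform from 0 to *U* days. The average share outside is *U*/60 for *U* up to 30, and 1 − 15/*U* beyond that.

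| Assumed range (days) | Calculation | Average share outside |
|---|---|---|
| 0-14 | 14/60 | 23% |
| 0-28 | 28/60 | 47% |
| 0-42 | 1 − 15/42 | 64% |
| 0-56 | 1 − 15/56 | 73% |
| 0-84 | 1 − 15/84 | 82% |

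Under the widest assumption, (84 − 30)/84 = 64% of patients would have no post-operative day inside the window. Under the 0-14 and 0-28 day assumptions, none would.

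**Do other provisions close the gap?**

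- The late-event clause in 10.3.2 covers events that are both serious and judged related. Late non-serious events stay outside.
- The vocal-cord examination (7.4.3) is required whatever the scan date, but it concerns the nerve only and is done before discharge.
- The text on follow-up at 1 and 6 months (7.4.3, 7.4.4) names blood tests. It does not ask for infection, haematoma or voice change.
- Section 10.3.3 declares no adverse events of special interest, so complications get no separate route there.
- The flow chart does cover the whole period, but it conflicts with section 10.

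**The case against.** A reader might infer that adverse events are recorded only to day 30 and that most complications will be lost. The documents do not support that. The flow chart schedules adverse events to six months after surgery. The complications are a secondary endpoint in their own right, and nothing says they are drawn from the adverse-event log. Section 14.1 requires everything the protocol asks for to be entered in the case report form and each missing item explained. The costs in section 9 are not tied to section 10 either. All of this stands, and it makes under-recording a possibility rather than a consequence.

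The late-event clause also reaches events related to the study procedure, and section 10.3.1 does not define treatment. If either term includes the operation, the gap narrows. It does not close: the clause remains limited to serious related events, and the only stated extension after treatment is still counted from the last drug.

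A reader might also infer a bias between arms, because patients needing a second scan could be unevenly distributed. That is speculative. A second injection restarts the 30-day clock. All examinations must also fall within 12 weeks before surgery and at least 48 hours apart, so a two-scan patient's last interval is at most 84 − 2 = 82 days. Such patients may be slightly better covered, if anything. Neither direction nor size can be established from the protocol.

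**Conclusion.** The point holds as a contradiction between operative rules. Sections 10.3.1 and 10.3.2 anchor recording to the tracer, the flow chart anchors it to surgery, and the section 10 window does not match the one-month complication endpoint.

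The result for a given patient follows from the protocol's own limits, with one month taken as 30 days: nothing of the post-operative month is inside the window once surgery is 30 or more days after the last tracer. The result for the trial as a whole is unknown, because it depends on an interval distribution the protocol does not give; the 23% to 82% range illustrates uniform intervals only. What is at risk is the capture of non-serious complications after discharge, and through it a secondary endpoint and part of the cost analysis. Actual loss, and bias between arms, are not shown.

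**What to change.** Reconcile sections 10.3.1 and 10.3.2 with the flow chart.

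1. Define the end of adverse-event recording relative to surgery, covering at least the one-month complication endpoint. State explicitly what is collected between 1 and 6 months, since the flow chart ticks adverse events at both.
2. Say whether the operation counts as treatment or as a study procedure for sections 10.3.1 and 10.3.2.
3. State in 7.4.3 that the complications listed in section 6.2 and section 9 are recorded at the existing 1- and 6-month contacts, present or absent, whatever the scan date.

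No visit or examination is added. The cost is a change of protocol wording, the matching case report form items, and slightly more adverse-event data entry.

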### 10.3.2 SAE reporting process

The investigator has to report the Sponsor of all serious adverse events occurring, once the informed consent form has been signed, **during treatment and 30 days after the last study drug administration.**

All late Serious Adverse Events and considered as reasonably related to the study treatment(s) or to the study procedure must be reported without delay limitation.

The investigator has to immediately report to the sponsor all serious adverse events with the exception of those that are identified as not requiring immediate reporting in the protocol or the investigator's brochure.

Pharmacovigilant contact : [[contact]](mailto:[contact])

[contact]

**This will be done by mailing sponsor's Serious Adverse Event Report Form, and it will be following by some report, as needed, containing all available information concerning the SAE.**

The investigator will specify for each event:

- ✓ The description as clear as possible according to the medical terminology,
- ✓ The intensity,
- ✓ The date of start and the date of end of the event,
- ✓ Measures taken and the necessity or not for a corrective treatment,
- ✓ If the treatment of the study was discontinued or if dose was modified
- ✓ The outcome: For a non-fatal event, the event should be followed until resolution or return to the initial status or to stabilization of potential sequels,
- ✓ The **causality assessment**: he has to assign a causality of "related to study treatment", if there is a "reasonable possibility" that the study treatment caused the event, or "not related to study treatment" if there is "no reasonable possibility" that the study treatment caused the event. The investigator must also assess whether the serious adverse event is "possibly related" to any study mandated procedure or activity, or others concomitants treatments, or under study or any others disease.

The investigator should also, when possible, attach to the serious adverse event report:

- ✓ A copy of the hospital report/hospitalization prolongation,
- ✓ A copy of the autopsy report,
- ✓ A copy of the results of all additional exams performed, including relevant negative results together with the range of normal laboratory values,
- ✓ Any other document judged useful and pertinent (including imaging)

All these documents should be **anonymized**.

Additional information may be requested by the sponsor.

The investigator should document the event as best as possible, provide medical diagnosis where possible and establish a causal link between the serious adverse event and the research, the study treatment, the associated drugs, an underlying pathology, progression of the disease or other cause.

The investigator shall promptly provide the sponsor with additional information regarding serious adverse events as he becomes aware of them.

The investigator should follow the patient who has had a serious adverse event until resolution, stabilization at a level acceptable to the investigator or return to the previous status, even if the patient withdraws from study and inform the sponsor of the serious adverse event outcome.

